### Missing data

Missing data will be reported for each variable individually and will be transparently documented for all variables included in the analysis, and reported as part of the descriptive results. Within the electronic case report form (eCRF), participants are given the option to select an “unknown” category where applicable, thereby allowing explicit capture of non-available responses at the point of data entry. Responses documented as “unknown” will be reported descriptively and treated as missing for analyses requiring classification of a risk factor as previously known, unknown, controlled, or insufficiently managed.

No formal imputation of missing data is planned given the exploratory character of this pilot implementation study.

Participants without available confirmatory testing for the respective parameter will not be included in parameter-specific PPV or diagnostic accuracy calculations. Uptake of confirmatory testing and missing confirmatory results will be reported descriptively. For implementation questionnaires, domain scores will be calculated only if sufficient item-level data are available for the respective domain. Otherwise, the domain score will be treated as missing. No item-level imputation is planned.

For the participant-level completion rate, participants who provide informed consent and start the screening procedure will remain in the denominator; participants with incomplete subsequent screening procedures will be counted as not completed. For the primary NNS analysis, only participants with completed screening procedures will be included in the denominator. Participants with incomplete screening procedures will therefore not contribute to the NNS analysis, but their number will be reported through the completion-rate outcome.

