### Primary outcomes

The study will assess three primary outcomes:

(I)Participant-level feasibility is assessed by screening completion rates of participants who provided informed consent. The outcome is defined as completion of the structured questionnaire, performance of blood pressure measurement and PoC-testing for dyslipidemia and HbA1c. The study aims for an overall completion rate ≥ 70% based on the reported use of primary care screenings and prospective feasibility on the national level in Germany.(II)Implementation outcomes from the pharmacy perspective are evaluated for the implementation domains acceptability, feasibility, and sustainability. The outcome is evaluated using validated instruments, including the Acceptability of Intervention Measure (AIM), the Feasibility of Intervention Measure (FIM), and the Normalization Measure Development Questionnaire (NoMad) to assess sustainability (Supplementary Tables 1 and NoMad Questionnaire) [16–19]. These instruments use standardized self-administered questionnaires completed by pharmacy staff that are rated on Likert scales. Validated German versions will be used. For each domain, the outcome criterion is defined by a null hypothesis assuming a median Likert-scale score ≤ 3. Rejection of the null hypothesis will be interpreted as evidence of sufficient implementation performance under routine practice conditions.(III)The medical screening yield is quantified by the number needed to screen (NNS) to identify at least one previously unknown or insufficiently managed CKM syndrome risk factor. These are defined as non-HDL cholesterol ≥ 5.7 mmol/L for known dyslipidemia or lipid-lowering therapy, HbA1c ≥ 8.5% in participants with known diabetes mellitus, positive albuminuria test without RASi or SGLT2i therapy in participants with CKD, or blood pressure ≥ 140/80 mmHg for participants with known hypertension. A NNS ≤ 5 will be considered as indicative of a clinically meaningful detection efficiency of the multi-parametric screening approach. Further, a NNS between 5 and 10 will be considered an exploratory finding indicating the need for potential refinement or modification of the screening strategy. An observed NNS > 10 will be interpreted as an unfavorable feasibility outcome under routine practice conditions.

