### Data source and collection at screening

In the initial visit, written informed consent will be obtained by the pharmacist and relevant data will be documented using an electronic case report form (eCRF). Table 2 displays the data collected at different time points. Subsequently, participants undergo standardized PoC assessments including albuminuria, blood pressure, HbA1c and full lipid profile (total cholesterol, non-high-density lipoprotein (non-HDL-C) cholesterol, HDL cholesterol (HDL-C), low-density lipoprotein cholesterol (LDL-C) and triglycerides). In pharmacies equipped for on-site PoC testing of albuminuria and blood pressure, all tests will be conducted at the initial visit. Alternatively, patients will be provided with validated home blood pressure monitors and semi-quantitative albuminuria tests along with instructions for testing. Results will be assessed in a second appointment in the pharmacy, together with PoC testing for HbA1c and lipid profile.

**Table 2 Tab2:** Data collected within the eCRF

Category	Data collected		
	At Screening	At Confirmatory Testing	At Follow-Up
Demographic data	• age • gender • postal code • educational level • employment status • type of health insurance		
History	• currently prescribed medication list • pre-existing medical conditions • family history of cardiovascular disease • smoking status • last participation in a health check-up		• medication • visits to the general practitioner after screening findings and therapy • changes from the GP visit • satisfaction with screening / self-assessed benefit of the project
Clinical	• home blood pressure (3x) • body weight • body height • calculated BMI • waist circumference	• 24-hour blood pressure	
Laboratory	• HbA1c • lipid profile (total cholesterol, non-HDL-cholesterol, calculated LDL, HDL, triglycerides) • albuminuria (albuminuria test or urine-albumin-creatinine-ratio)	• HbA1c • fasting plasma glucose • lipid profile (total cholesterol, LDL, HDL, triglycerides, lipoprotein(a)) • creatinine, cystatin c • urine-albumin-creatinine-ratio	

GP, General Practitioner; HDL, high-density lipoprotein; LDL, low-density lipoprotein, BMI, body mass index

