Implementation outcomes will be analyzed separately for each implementation instrument and domain. AIM, FIM, and NoMad assess conceptually distinct implementation constructs, including acceptability, feasibility, and normalization/sustainability. Therefore, no combined implementation score or omnibus test will be used. For each domain, median Likert-scale scores and interquartile ranges will be reported. In addition, one-sided one-sample Wilcoxon signed-rank tests will be used to assess whether domain scores exceed the neutral midpoint of the scale, using the null hypothesis that the median domain score is ≤ 3. Given the exploratory nature of this pilot implementation study and the domain-specific interpretation of implementation outcomes, no formal multiplicity adjustment is planned. Results will be interpreted separately by domain and in the context of the overall implementation pattern.

The unadjusted NNS will be calculated as the number of participants with completed screening divided by the number of participants with at least one previously unknown or insufficiently managed CKM risk factor identified during screening. For primary outcome, a pre-specified PPV-adjusted NNS will be calculated using the positive predictive value estimated among screen-positive participants undergoing confirmatory testing at the study center. Participants without available confirmatory testing will not be included in the estimation of the PPV. Stratified NNS according to pharmacy-prompted or self-referral recruitment will be further reported.

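### Treating an unknown history as missing can remove from the NNS participants whose event status the measured value already settles

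*Protocol article*

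**What the plan says.** The Missing data section of the protocol article explains that in the eCRF "participants are given the option to select an “unknown” category where applicable". Such answers are reported descriptively and "treated as missing for analyses requiring classification of a risk factor as previously known, unknown, controlled, or insufficiently managed". The same section adds: "No formal imputation of missing data is planned given the exploratory character of this pilot implementation study".

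Under Sample size and statistical analysis, the unadjusted NNS is the "number of participants with completed screening divided by the number of participants with at least one previously unknown or insufficiently managed CKM risk factor" found at screening. On the denominator, the Missing data section states that "only participants with completed screening procedures will be included in the denominator". It does not say what happens to a participant who completed screening but whose risk factor could not be classified.

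The criteria stand in two places. Primary outcomes defines insufficient management in people with a known condition, for example "non-HDL cholesterol ≥ 5.7 mmol/L for known dyslipidemia or lipid-lowering therapy". Confirmatory testing gives the general screening thresholds. Table 2 shows that pre-existing conditions and the "currently prescribed medication list" are both recorded at screening.

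**The concern.** The NNS is one of three primary outcomes and is read against fixed lines at 5 and 10. Its numerator is a union: a factor counts if it is previously unknown or if it is known and insufficiently managed. A participant who answers *unknown* to, say, prior hypertension and has a systolic pressure of 150 mmHg is an event under either history. The rule nevertheless sets that factor to missing, because it names the categories from which the numerator is built.

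*Unknown* is a permitted answer, so the questionnaire is complete and the participant belongs to the completed-screening denominator. On the literal text the person is counted below the line and cannot be counted above it through that factor. A result close to 5 could then be reported in the wrong category because of a data-handling rule.

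**Working it through.** **Plan's own figures.** NNS 5 corresponds to 1/5 = 20% of those screened, and 5 × 20 = 100 to 5 × 30 = 150 for the downstream NNS. Both match Primary outcomes. The expected 250 participants with an indication for confirmatory testing is 10 pharmacies × 50 × 0.50, which matches Sample size and statistical analysis.

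**Does history change event status?** Known-condition criteria are from Primary outcomes. For a condition not known, the thresholds in Confirmatory testing are assumed to define a previously unknown factor, since no separate definition is given. The blood pressure criterion of 140/80 is read as either component.

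| Finding | Event if known | Event if not known | History needed |
|---|---|---|---|
| non-HDL-C ≥ 5.7 mmol/L | yes | yes | no |
| HbA1c ≥ 8.5% | yes | yes | no |
| HbA1c 5.7 to < 8.5% | no | yes | **yes** |
| Systolic ≥ 140 or diastolic ≥ 90 mmHg | yes | yes | no |
| Diastolic 80–89, systolic < 140 mmHg | yes | no | **yes** (texts differ) |
| Positive albuminuria, no RASi/SGLT2i | yes | yes | no |
| Positive albuminuria on RASi/SGLT2i | no | yes | **yes** |
| Below both criteria | no | no | no |

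The diastolic row exists only because Primary outcomes uses 140/80 and Confirmatory testing uses 140 and/or 90. The two passages must be reconciled.

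**Size on the literal reading.** Let p be the true yield and u the share of event participants whose every qualifying factor has an unknown history. Missingness works per factor, so someone who qualifies through another factor is not lost. Then NNS = 1/[p(1 − u)], i.e. the true NNS times 1/(1 − u). The documents give no value for u; 5–15% is assumed.

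- p = 0.21 (assumed, chosen beside the threshold; true NNS 1/0.21 = 4.76): 1/(0.21 × 0.95) = 5.01; 1/(0.21 × 0.90) = 5.29; 1/(0.21 × 0.85) = 5.60.
- p = 0.50 (the protocol's expected prevalence; true NNS 2.00): 1/(0.50 × 0.95) = 2.11; 1/(0.50 × 0.85) = 2.35. Reaching 5 would need 1 − u = 1/(0.50 × 5) = 0.40, so u = 60%.

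**PPV adjustment.** The primary NNS is PPV-adjusted; taking this as NNS/PPV (assumed) with p = 0.50, no loss gives 5 at PPV = 1/(0.50 × 5) = 0.40. With u = 15% it is reached at PPV = 1/(0.50 × 0.85 × 5) = 0.47. The rule would then change the verdict only for a PPV between about 0.40 and 0.47.

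**Does the denominator matter?** Illustration (all counts assumed): 1000 completed, 100 with an unknown history on a decisive item, 180 events among the other 900.

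- Kept in the denominator, not countable: 1000/180 = 5.56.
- Dropped from both: 900/180 = 5.00.
- Truth if 30 of the 100 are events: 1000/210 = 4.76. If 10 are: 1000/190 = 5.26.

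Keeping them in the denominator overstates the NNS in both cases. Dropping them overstates it in the first case (5.00 against 4.76) and understates it in the second (5.00 against 5.26).

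**What the correction gives.** If 30 of the 100 are settled events, 50 settled non-events and 20 history-dependent, the NNS lies between 1000/(210 + 20) = 4.35 and 1000/210 = 4.76. Recovering only the events and dropping the 50 settled non-events would give (1000 − 70)/210 = 4.43, against (1000 − 20)/210 = 4.67 with them kept. Non-events must therefore be classified by value too.

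**The case against.** The strongest reply is that the rule is conditional: it applies to analyses that require classification, and a value above both criteria requires none. That reading is possible. However, the document does not adopt it, and the numerator, "at least one previously unknown or insufficiently managed CKM risk factor identified during screening", is worded in the rule's own terms. An analyst following the text could reasonably set these factors to missing.

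Other objections stand and limit the point:

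- A reader might infer that the loss always inflates the NNS. That holds only if the affected participants stay in the denominator. This is the natural reading, but the text does not exclude dropping them.
- A reader might infer that someone who answers *unknown* is a newly detected case. The Missing data section describes the option as capturing non-available responses, which can include a diagnosis the participant does not recall. Counting all such people as new detections would favour success.
- The effect near the threshold is small against sampling error. At 21% and n = 1000, the 95% interval is 0.21 ± 1.96 × √(0.21 × 0.79/1000), about 18.5–23.5%, or an NNS of 4.25–5.41. Unlike sampling error, though, this bias does not shrink with more participants.

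It can also be said that derivation rules belong in an analysis plan that is not shown. Here, however, the protocol has itself fixed a rule, and that rule can give a wrong answer.

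**Conclusion.** The point holds in limited form. As written, the missing-data rule can discard outcomes that the measured value already determines, in the numerator of a primary outcome. On the literal denominator this inflates the NNS by 1/(1 − u).

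The size cannot be derived from the documents, because the share of unknown answers is not given. With u assumed at 5–15%, the category changes only if the NNS is already near 5: an assumed yield of 21% moves from 4.76 to 5.01–5.60. At the 50% in the sample-size section the unadjusted NNS stays at about 2.1–2.4. A reader might infer that the trial's conclusion is in danger; the protocol's own planning figure does not support that, unless the PPV is low enough to bring the adjusted NNS close to 5.

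The conclusion assumes that the Confirmatory testing thresholds define a previously unknown factor. It does not extend to every participant with an unknown history, since three kinds of finding depend on history as the texts stand.

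**What to change.** For the NNS, replace the blanket rule with the following:

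1. Where the measured value gives the same answer under both histories, classify it by value, as an event or as a non-event.
2. State that all participants with completed screening stay in the denominator, whatever their history answers.
3. Treat only history-dependent values as unresolved: HbA1c 5.7 to < 8.5%, positive albuminuria under RASi/SGLT2i and, until Primary outcomes and Confirmatory testing are reconciled, diastolic 80–89 mmHg with systolic < 140 mmHg. A participant with another settled event counts anyway.
4. Report the NNS twice, with participants who remain unresolved counted as events and as non-events.
5. Optionally, add a sensitivity analysis that resolves unknown history from the medication list. For lipids the protocol already treats lipid-lowering therapy like a known condition.

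This is a derivation rule on data already in the eCRF and can be set before analysis, with no new procedure. The costs are that the NNS becomes a range, which may be wide if many values are unresolved, and that the medication list is an imperfect proxy for a diagnosis, which is why it should only support the main result.

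### Primary outcome I has two denominators (all who consented; those who consented and started screening), and the narrower one, with the start undefined, can only raise the completion rate

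*Protocol article*

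**What the plan says.** Primary outcomes, item (I), bases participant-level feasibility on "screening completion rates of participants who provided informed consent". Completion means "completion of the structured questionnaire, performance of blood pressure measurement and PoC-testing for dyslipidemia and HbA1c". The target is an overall rate of at least 70%. Consent is the only condition for entering the denominator.

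Missing data returns to the same outcome and says that "participants who provide informed consent and start the screening procedure will remain in the denominator". It adds that "participants with incomplete subsequent screening procedures will be counted as not completed". Entry now needs two things, consent and a start.

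Data source and collection at screening gives the order of events: "In the initial visit, written informed consent will be obtained by the pharmacist", with data entered in the eCRF at that visit and the point-of-care tests after that. Where albuminuria and blood pressure are not tested on site, participants take devices home: "Results will be assessed in a second appointment in the pharmacy, together with PoC testing for HbA1c and lipid profile".

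The start of screening is not defined anywhere in the article. Nor does the article say what happens to a participant who consents and does not start.

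**The concern.** A primary outcome with a pass mark needs one denominator. Here the article states two in its current text, and they differ whenever at least one consented participant does not start. This is not detail left to an analysis plan, because both versions are written down.

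The difference runs one way. Anyone who never starts cannot have completed, so removing that person shrinks the denominator and leaves the numerator unchanged. The reported rate can only rise.

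The Missing data section also keeps participants with incomplete screening out of the number-needed-to-screen analysis, on the ground that the completion-rate outcome will show how many there were. A consented non-starter who is left out of the completion rate as well would appear in neither analysis, so that safeguard would not reach this group.

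The Limitations section makes demonstrated feasibility, together with sufficient diagnostic yield, the condition for a larger study. In a single-arm study with two published denominators, the choice between them could be made after the data are known.

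**Working it through.** **The plan's own figure.** The 70% target is a benchmark set by the authors. No calculation lies behind it, so there is nothing to reproduce.

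**Inputs**
- N = 1,000 participants (Study setting and pharmacy selection: 20 pharmacies × 50). I take all 1,000 as consented.
- Target: 70% (Primary outcomes).
- s, the share of consented participants who never start: not in the documents. Assumed values: 2%, 5%, 10%.
- C, the number of completers: not in the documents. One illustrative value is used below and is labelled as such.

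**Formulas**
- Rate under Primary outcomes: C / N.
- Rate under Missing data, if non-starters are left out: C / [N(1 − s)].
- Ratio of the second to the first: 1/(1 − s), which is at least 1.

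**What an observed 70% among starters means for all consented**

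| Assumed s | Starters | Completers giving 70% of starters | Rate among all consented | Gap |
|---|---|---|---|---|
| 2% | 980 | 0.70 × 980 = 686 | 68.6% | 1.4 points |
| 5% | 950 | 0.70 × 950 = 665 | 66.5% | 3.5 points |
| 10% | 900 | 0.70 × 900 = 630 | 63.0% | 7.0 points |

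The reading against the target changes whenever the all-consented rate lies from 0.70(1 − s) up to just under 0.70. At s = 5% that is from 66.5% to just under 70%.

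**Scale against sampling error.** The simple 95% half-width at p = 0.70 and n = 1,000 is 1.96 × √(0.70 × 0.30 / 1,000) = 2.8 points, ignoring clustering by pharmacy. The Sample size section quotes about ±5%. The gap at s = 2% is below both. At s = 5% it exceeds the first only, and at s = 10% it exceeds both.

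**Illustration, with an assumed C = 650.** The all-consented rate is 650/1,000 = 65.0%, below target. The started-only rate is:
- s = 2%: 650/980 = 66.3%
- s = 5%: 650/950 = 68.4%
- s = 10%: 650/900 = 72.2%

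The crossing point is N = 650/0.70 = 928.6, so 72 non-starters suffice: 650/928 = 70.04%. Neither 650 nor 72 is a forecast.

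**Who could be a non-starter?** The sections, read together, give two groups:
1. *Consents, then stops before any data entry or test.* A failure under Primary outcomes. Outside the denominator under the wording of Missing data.
2. *Consents, has eCRF data entered, takes devices home, misses the second appointment.* A failure under Primary outcomes. Under Missing data, a failure if eCRF entry or handing out devices counts as a start, which is the natural reading. Without a definition, it is not the only possible one.

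**The case against.** The strongest defence is that the Missing data sentence is there to retain people. It says who stays in the denominator and that incomplete cases count as failures. It nowhere says outright that consented non-starters are removed; that follows only from the added condition. If the questionnaire always begins directly after consent and counts as the start, the two denominators nearly coincide. In addition, the 70% is an aim, the analysis of this outcome is descriptive with no test attached, the study calls itself an exploratory pilot, and completion is also summarised by pharmacy.

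Much of this stands. It limits the severity and the number of people likely to be affected. It does not reconcile the two sentences, because the article does not say that the questionnaire marks the start.

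A reader might infer something stronger: that people at the ten pharmacies without on-site urine testing, about 500 participants, can consent, fail to return and disappear from the outcome, so that the rate is inflated mainly where feasibility is most in doubt. The documents do not support that. Data are entered in the eCRF at the consent visit, Table 2 lists demographic and history items as collected at screening, and the questionnaire is itself a component of completion. A person sent home with screening devices has, on the natural reading, started, and a missed second appointment is then an incomplete procedure counted as a failure. Nor do the documents show that non-return is the main way the two-visit route fails. Expressing the 72 non-starters as about 14% of those 500 (72/500 = 14.4%) rests on the disputed reading and should not be used.

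**Conclusion.** The inconsistency holds. One primary outcome, read against a 70% target, has two stated denominators, and the word that separates them is undefined. The narrower one can only raise the rate, by the factor 1/(1 − s). The size is conditional: under assumed non-start shares of 2%, 5% and 10%, a reported 70% would stand for 68.6%, 66.5% and 63.0% of all consented. If almost everyone begins the questionnaire at the consent visit and that counts as the start, s is close to zero and the effect is negligible.

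Severity is moderate. The definition of a primary outcome is affected and the direction of bias is known, but the size is not, and the largest plausible group of drop-outs is most naturally already counted as not completed.

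**What to change.** In Missing data, remove the condition that the participant must also have started screening, so that the denominator matches Primary outcomes. Wording along these lines would do:

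> The denominator for the completion rate is every participant with signed informed consent. Consented participants who never start, who do not return for a second appointment, or who leave any required component undone are counted as not completed.

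Then define the start of screening once (for example, the first eCRF entry after consent), report how many consented but did not start, and give the started-only rate as a descriptive figure beside the primary one.

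The cost is one phrase and a short definition. The 70% target stays as it is, and the only new item is a count of signed consents without a start. The reported completion rate may be slightly lower than under the narrower denominator.
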